# Effects of a multi-level intervention on the pattern of physical activity among in-school adolescents in Oyo state Nigeria: a cluster randomised trial

**DOI:** 10.1186/s12889-017-4781-y

**Published:** 2017-10-23

**Keywords:** Self-reported physical activity, Objectively measured physical activity, Physical fitness, In-school adolescents, Multi-level intervention

## Abstract

**Background:**

Physical inactivity contributes to the global burden of non-communicable diseases. The pattern of physical activity in adulthood are often established during adolescence and sedentary behaviours in the early years could influence the development of diseases later in life. Studies on physical activity in Nigeria have focused largely on individual behaviours and the effects of school-based interventions have not been well investigated. The aim of the proposed study is to identify factors influencing; and evaluate the effects of a multi-level intervention on the physical activity behaviours of in-school adolescents in Oyo state, Nigeria.

**Methods:**

The study will adopt a cluster randomised controlled trial design and schools will serve as the unit of randomisation. The sample size is 1000 in-school adolescents aged 10–19 years. The study will be guided by the socio-ecological model and theory of reasoned action and baseline data will be obtained through a mixed methods approach comprising a cross sectional survey to document the self-reported physical activity levels coupled with objectively measured physical activity levels using pedometers for a subset of the sample. Other measurements including weight, height, waist and hip circumferences, fitness level using the 20-m shuttle run test (20-mSRT) and blood pressure will be obtained. The schools’ built environment and policy support for physical activity will be assessed using structured questionnaires coupled with key informant interviews and focus group discussions with the school authorities. Baseline findings will guide the design and implementation of a 12-week multi-level intervention. The primary outcome measures are self–reported and 7-day objectively measured physical activity. Other secondary outcome measures are body-mass-index for age, waist-to-hip ratio, cardioresiratory fitness and blood pressure. The association between behavioural factors and physical activity levels will be assessed. Follow-up measurements will be taken immediately after the intervention and 3-months post intervention.

**Discussion:**

Physical activity behaviours of adolescents in Nigeria are influenced by multiple factors. There is an urgent need for effective school-based interventions with a potential to improve the physical activity behaviours of adolescents in Nigeria and other low and middle income countries.

**Trial registration:**

Pan African Clinical Trial Registry. Trial registration number: PACTR201706002224335, registered 26 June 2017.

## Background

Nigeria, a developing country with a population of 170 million and a third of its populace in the 10–24 years age group contributes significantly to the global burden of non-communicable diseases (NCDs) [1, 2]. According to the Global Status Report on Non-communicable diseases, Nigeria had an estimated 792,600 NCDs related deaths in 2008 and this high mortality figure is linked to four modifiable risk factors namely *physical inactivity, unhealthy diets, tobacco and harmful alcohol use* [2]. These risk factors are typically initiated during adolescence and set the stage for unhealthy behaviours which persist into adulthood and diseases later in life [3].

According to the National Strategic Framework on the Health and Development of Adolescents and Young People in Nigeria, there is a gradual increase in the number of physically inactive, overweight, young children and adolescents in Nigeria [4]. Obesity in childhood and adolescence has been linked to cardiovascular diseases, type-2 diabetes, cancer and depression [5–8]. Findings from recent studies conducted among adolescents in different Nigerian states lend credence to the growing epidemic; the reported prevalence of overweight and obesity among adolescents in Benue state was 9.7% and 1.8% [9]; 13.8% and 9.4% in Lagos state [10] and 5.8% and 1.1% in Ondo state [11] respectively.

Compared to other developed regions of the world, the reported prevalence of obesity among adolescents in Nigeria is low however; this is rapidly increasing due to the corresponding rise in the behavioural antecedent risk factors specifically *unhealthy diets and physical inactivity*. A study by Odunaiya et al., (2010) among in-school adolescents in Oyo State, Nigeria found that, 38%, 58.8% and 3.2% engaged in low, moderate and high intensity physical activity behaviours respectively [12]. Furthermore, 8.8% were overweight and 1.2% were obese and body mass index was inversely associated with physical activity levels. Adeniyi et al. (2011) also found a significant level of physical inactivity among students in Ibadan, Oyo State and this was linked to individual and school factors [13]. According to Adeniyi et al, the physical activity levels of the participants varied; 53.8%, 38.8% and 7.4% engaged in low, moderate and high intensity physical activity behaviours respectively [13]. Physical inactivity was higher among students in private schools and associated with depression. The increasing level of physical inactivity in Nigeria and many other countries in the world is largely due to motorisation, urbanisation, automation of daily activities and greater opportunities for sedentary behaviours and underscores the need to address this growing burden [14–16].

In 2013, the World Health Assembly endorsed a resolution calling upon member states to address the needs of the youth by prioritising the surveillance of trends and determinants of non-communicable diseases and adopting a lifecourse approach in its prevention and control [17]. Evidence points to adolescence as a crucial period in the development of NCDs and underscores the need to institute or intensify surveillance of risk factors and implement population wide interventions to reduce the morbidity and mortality associated with these diseases. Schools have been identified as a setting for influencing the physical activity behaviours of young people but several factors influences its role in this regard. Numerous recommendations have been proposed to address physical inactivity and unhealthy diets within the school setting however; most of these strategies have targeted the individual level resulting in relatively modest changes in behaviours.

There is a global call to address the root cause of unhealhy diets and physical inactivity by implementing population wide interventions within health promoting setting such as schools and workplaces and this requires profound policy changes and leadership support [15]. In order to reduce the impact of the major risk factors for NCDs, the World Health Assembly adopted the Global Strategy on Diet, Physical Activity and Health and the School Policy Framework on Diet and Physical Activity [18]. Paragraph 49 of this document states that*: “School policies and programmes should support the adoption of healthy diets and physical activity. Schools are encouraged to provide students with daily physical education and should be equipped with appropriate facilities and equipment. Governments are encouraged to adopt policies that support healthy diets at school and limit the availability of products high in salt, sugar and fats”*. The extent of implementation of this initiative in Nigeria is currently low.

A systematic review of few studies conducted in high income countries found strong evidence that multi-component interventions and policies were effective in promoting physical activity among students [19]. However; this intervention has not been tested in Nigeria. A study conducted by Gillis et al. (2013) among international physical activity experts using a twin-panel Delphi methodology ranked *policy and/or environmental change and their influence on children’s physical activity and sedentary behaviours* second on the list of 29 international research priorities on child and adolescent physical activity behaviours [20]. This underscores the justification for this study. Research studies on the physical activity behaviours of young people in Nigeria have focused solely on individual behaviours [12, 21] without analyzing critically, the influence of social-cultural, institutional, environmental and policy level factors resulting in an unbalanced attention to individualised behaviour change strategies instead of a true public health intervention which requires systems approach [22]. These underscore the importance of this study which is designed to identify the socio-ecological factors (*individual, social, built environment and policy*) influencing the physical activity behaviours of in-school adolescents and to evaluate the effect of a multi-level intervention on the physical activity and fitness levels of in-school adolescents in Oyo state, south western Nigeria.

## Methods

### Study research design

The proposed study will utilise a cluster randomised trial design to test the effect of a 12-week multi-level intervention on the physical activity and fitness levels of in-school adolescents aged 10–19 years in twenty two public and private-owned secondary schools in Oyo state, south western Nigeria. Secondary schools will be the unit of randomisation, and these will be assigned to the multi-level intervention or control arm (no intervention) with longitudinal data collection for index or cohort children randomly selected from the student population. Prior to the experimental study, preliminary data will be collected on the physical activity behaviours of in-school adolescents and the socio-ecological factors influencing the school physical activity environment. This will guide the design of a multi-level, multi-component intervention which will run for 12 weeks with assessments conducted at baseline, post-intervention and at 3-months follow-up. The design, conduct and reporting of this study will adhere to the Consolidated Standards of Reporting Trials (CONSORT) guidelines. Ethical approval was obtained from the Oyo State Research Ethical Review Committee (AD13/479/890) and permission from the Oyo State Ministry of Education. The trial is registered with the Pan African Clinical Trial Registry.

### Study site

The study sites are Ibadan and Ogbomosho, urban cities located in Oyo State, the South-West geopolitical region of Nigeria. It is one of the three States carved out of the former Western region of Nigeria in 1976. Oyo State consists of 33 Local Government Areas. The State covers a total of 27,249 km^2^ of land mass and has a population of about 4.5million. The people of Oyo State may be divided into five broad groups which are: Ibadan, Ibarapa, Oyo, Oke-Ogun and Ogbomoso. The state has four universities, (one federal government university, a state government university and two private universities); four polytechnics (one state government owned and three private polytechnics) and over 500 public and private secondary schools (Fig. 1).

**Fig. 1 Fig1:**
[figure not shown]
CONSORT flowchart describing progress of participants through the study

### Study population

The study population are in-school adolescents (10–19 years) in co-educational public and private schools. In addition, officials of the Ministry of Education and School Principals will be interviewed using a key informant interview guide while Physical and Health Education Teachers will complete semi-structured questionnaires. Focus group discussions will be held with Classroom Teachers.

#### Inclusion Criteria

In-school adolescents in public and private schools

#### Exclusion Criteria

Out-of-school youthsAdolecents in schools for the disabled

### Sample size for the intervention study

The minimum sample size for this study was obtained using the formula for calculating sample size for two proportions with the aim of detecting a difference in outcomes between the groups [23]. The effect size of a similar study which was conducted in Denmark [24] and the prevalence of moderate and high intensity physical activity reported by Odunaiya et al., 2010 [12] were used for calculating the minimum sample size. A multi-level intervention to promote physical activity among in-school adolescents has not been conducted in Nigeria and the effect size is unknown. This justifies the use of the value reported in Denmark [24]. A *multilevel intervention is defined as an intervention* that addresses at least three levels of the multilayer system. It target at least three sources of influence that may ultimately result in improved health behaviour and outcomes [25].

Intracluster correlation coefficient (ICC) is a measurement that captures between-cluster and within-cluster variability in outcome and is required for sample size calculation in clustered studies that comprise exposed or unexposed clusters [26–29]. To account for this, the intracluster class correlation reported by Oyeyemi et al., (2014) which assessed participants’ self-reported active transportation to school and leisure-time Moderate-to-Vigorous Physical Activity (MVPA) among in-school adolescents was used to estimate the within and between school variation in physical activity in order to control for clustering within the schools (ICC = 0.38) [30]. The formula is outlined below:$$ \mathrm{n}=\frac{{\left({Z}_{\alpha /2+}{Z}_{\beta}\right)}^2\left[{\mathrm{P}}_1\left(\ 1-{\mathrm{P}}_1\right)+{\mathrm{P}}_2\left(\ 1-{\mathrm{P}}_2\right)\right]}{{\left({\mathrm{P}}_{1\hbox{--} }{\mathrm{P}}_2\right)}^2}\times \left[1+\left({\mathrm{m}}_{\mathrm{o}}-1\right)\times \mathrm{ICC}\right]. $$where Z_α/2_ is the critical value of the normal distribution at α/2 (e.g. for a confidence level of 95%, α is 0.05 and the critical value is 1.96), Z_β_ is the critical value of the normal distribution at β (e.g. for a power of 80%, β is 0.2 and the critical value is 0.84) and P_1_ and P_2_ are the expected sample proportions of the two groups.

Z_α/2_ = 1.96 at 5% level of error.

Z_β_ = 0.84

P_1_ = 62% i.e. the proportion of the participants in the unexposed (control) group who are either moderately or vigorously physically active *(58.8% engaged in moderate physical activity levels while 3.2% engaged in high physical activity levels based on the study by Odunaiya, et al., 2010)* [12].

P_2_ = 72% i.e. the proportion of the participants in the exposed (experimental) group who are expected to become physically active 12 weeks after the intervention. This translates to the effect size i.e. 10% increase in the outcome measure of physical activity at follow up [24].

*ρ* = 0.38 [30].

The design effect or variance inflator factor = [1+ (k-1) x*ρ*

k = approximately the average number of individuals to be sampled per cluster. This will be 50 per school.

Three hundred and thirty six per group is the minimum sample size needed to detect whether the stated difference exists between the two proportions. A total of one thousand in-school adolescents will be selected for the study (500 for the control and 500 for the experimental group) to account for loss to attrition and increase the precision for the point estimate for physical activity behaviours among the adolescents.

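### The stated minimum of 336 per group omits the protocol's own design effect; at its ICC of 0.38, 22 schools and 1,000 students give about 12% power for 62% versus 72%, not 80%

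*Protocol article*

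**What the plan says.** The section Sample size for the intervention study of the protocol article sizes the trial with a two-proportion formula multiplied by a bracket, 1 + (m₀ − 1) × ICC.

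- **Error rates:** "Z_α/2_ = 1.96 at 5% level of error", and a Z for β of 0.84, explained by the example "for a power of 80%, β is 0.2 and the critical value is 0.84".
- **Control proportion:** "P_1_ = 62% i.e. the proportion of the participants in the unexposed (control) group who are either moderately or vigorously physically active".
- **Intervention proportion:** "P_2_ = 72% i.e. the proportion of the participants in the exposed (experimental) group who are expected to become physically active". On the size of the effect: "This translates to the effect size i.e. 10% increase in the outcome measure of physical activity at follow up".
- **Clustering:** an ICC of 0.38 is taken from a cited study. The protocol says it "was used to estimate the within and between school variation in physical activity in order to control for clustering within the schools".
- **Cluster size:** "k = approximately the average number of individuals to be sampled per cluster. This will be 50 per school".
- **Result:** "Three hundred and thirty six per group is the minimum sample size needed to detect whether the stated difference exists between the two proportions".

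The section then raises the number to 500 per group, 1,000 in all, and gives attrition and precision as the reasons. The section Blinding and sampling technique fixes 11 schools in each arm.

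**The concern.** A design effect computed from an ICC of 0.38 and 50 students per school is close to 20. A result of 336 per group for a 10-point difference around 60 to 70% is about what an individually randomised trial would need. So the clustering adjustment appears in the formula and the text but not in the number.

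The section presents the trial as sized for its target difference with clustering taken into account. If that is untrue, a real 10-point benefit would probably go undetected, and a non-significant result would say little about whether the intervention works.

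**Working it through.** **Inputs, all from the protocol article.** Z values 1.96 and 0.84; P₁ = 0.62; P₂ = 0.72; ICC = 0.38; k = 50; 500 students and 11 schools per arm.

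**1. The protocol's own figure.** Without the bracket:

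- Variance term: 0.62 × 0.38 + 0.72 × 0.28 = 0.4372
- n = (1.96 + 0.84)² × 0.4372 / 0.10² = 342.8, so 343 per group

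The stated 336 is 2% below this. To obtain 336 from the full formula, the bracket would have to equal 336/342.8 = 0.98. With a positive ICC and more than one student per school the bracket exceeds 1, so it was not applied.

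**2. The full formula.**

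- Design effect: 1 + 49 × 0.38 = 19.62
- n = 342.8 × 19.62 ≈ 6,725 per group
- Schools: 6,725/50 ≈ 135 per arm

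The increase from 336 to 500 is a factor of 1.49, against the 19.62 required.

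**3. Power of the planned trial at ICC 0.38.** Fifty per school in 22 schools would be 1,100 students, not the planned 1,000, so the size implied by the totals is used here: 500/11 = 45.5 per school.

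- Design effect: 1 + 44.45 × 0.38 = 17.89
- Effective size: 500/17.89 = 27.9 per arm
- Standard error: √(0.4372/27.9) = 0.125
- Standardised difference: 0.10/0.125 = 0.80
- Power, two-sided 5%: 12.6% (normal) or 11.9% (t, 20 df, from 22 schools)

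Using 550 per arm at 50 per school gives the same 12.6% and 11.9%.

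**4. The limit set by 11 schools.** With unlimited students per school the effective size tends to 11/0.38 = 28.9 per arm. The standardised difference is then 0.10/√(0.4372/28.9) = 0.81 and power is 12.9% (normal).

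**5. Detectable difference.** At ICC 0.38, 62% versus 92% (30 points) has 81% power by the normal approximation and 77% by t. By t, 62% versus 93% (31 points) has 81%.

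**6. Power for 62% versus 72% at other ICCs** (assumed values; 500 students in 11 schools per arm):

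| ICC | Design effect | Power, normal | Power, t (20 df) |
|---|---|---|---|
| 0.38 | 17.89 | 13% | 12% |
| 0.20 | 9.89 | 19% | 18% |
| 0.10 | 5.45 | 31% | 28% |
| 0.05 | 3.22 | 47% | 43% |
| 0.02 | 1.89 | 69% | 65% |
| 0.01 | 1.44 | 80% | 76% |

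The ICC at which 500 per arm just meets the protocol's formula is (500/342.8 − 1)/44.45 = 0.0103. By t, 80% needs an ICC of about 0.007.

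**The case against.** There are four fair points on the other side.

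- **The ICC may not be the right one.** It comes from a cited study of active transport to school and leisure-time activity, and the protocol does not show that it is the between-school coefficient for the dichotomised outcome used here. This stands: 12% is the power at the protocol's own ICC, not necessarily the true power. It does not rescue the claim, because power is still below 50% at an ICC of 0.05.
- **The planned analysis is more efficient than the sizing formula.** The protocol plans mixed models for repeated measures with covariate adjustment, pair-matches schools, and allows a continuous activity score. These could raise power, so the 12% must be labelled as an unadjusted follow-up comparison. The protocol gives no baseline correlation or gain from matching. As an assumption, if baseline adjustment multiplies the variance by 1 − r², then r = 0.5, 0.8, 0.9 and 0.95 give about 15%, 27%, 45% and 73% at ICC 0.38 (normal). All fall short of 80%.
- **The protocol never states the power achieved with 1,000 students.** True. The 80% is implied by the Z of 0.84 and its gloss.
- **The protocol sets no rule for reading a null result.** Also true. Misreading one is a risk, not something the plan commits to, and a sentence on interpretation is optional.

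None of these affects the arithmetic: the stated formula and inputs do not give 336.

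**Conclusion.** The concern holds. The stated minimum is a sample size for individual randomisation, about 2% low even for that, and roughly one twentieth of what the protocol's formula gives (336 against 6,725 per group). With 11 schools and 500 students per arm, power for a 10-point difference is about 12% at the stated ICC, so a true effect of that size would be missed about seven times in eight.

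That power figure assumes a between-school ICC of 0.38 for the binary outcome, equal cluster sizes, no attrition, and an unadjusted comparison at follow-up, which is the protocol's own basis for sizing. A smaller ICC or strong baseline adjustment would improve it. No adjusted scenario tested at the stated ICC reached 80%.

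**What to change.** Rewrite the end of the sample-size section as follows.

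1. Give 343 per group as the unclustered size, and 6,725 per group as the result of the printed formula with ICC 0.38 and 50 per school. Reconcile 50 per school with 1,000 students in 22 schools.
2. Confirm that 0.38 is a between-school ICC for this outcome. If it is not, replace it with a justified value and restate the calculation.
3. State the power of 22 schools and 1,000 students for 62% versus 72%, labelled as an unadjusted follow-up comparison, with a power-by-ICC table and the detectable difference, using one method (normal or t) throughout. If credit is taken for baseline adjustment or matching, state the assumed correlation or gain.
4. Optionally, say that a non-significant result will be interpreted through its confidence interval and not as evidence of no effect.

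The cost is the rewording, a check of the ICC source, and a much less favourable power statement. No added enrolment is proposed.

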### Blinding and sampling technique

Multistage sampling technique will be used for the study. Nigeria is divided into six regions with approximately six states each. The south west region was purposively selected for this study.Step 1:The study state was selected randomly from the six states in the south west region of Nigeria.Step 2:Two comparable Local Government Areas (LGAs) in the project state will be selected using simple balloting. The list of LGAs was stratified based on their socio-economic status and level of urbanisation. One of the LGAs will be the experimental while the other will serve as the control.Step 3:The list of schools will be obtained for the selected LGAs and stratified by ownership i.e. public and private and population size. Twenty two schools will be pair-matched based on their ownership (i.e. public and private) and population size and randomly allocated to either the experimental (11 schools) or control (11 schools) group by simple randomisation by an independent researcher not involved in the study.Step 4:The male and female student ratio for the selected schools will be obtained and used for the determination of students to be selected for each school disaggregated by sex. The selected in-school adolescents will serve as the index children though all the students in the schools allocated to the experimental group will be exposed to the intervention.Step 5:The number of arms for classes from each school will be documented and two arms of classes at each level in the school will be selected by balloting for the study.Step 6:Study participants in each class will be selected using systematic random sampling technique based on the male to female student ratio and expected cluster size for the school.Step 7:The selected respondents will be enrolled as a cohort in the experimental and control schools and followed up after the 12-week intervention.

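### The sampling section gives two incompatible allocation rules, by LGA in Step 2 and by school in Step 3; if Step 2 is followed, there is one allocation unit per arm

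*Protocol article*

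**What the plan says.** The protocol article describes allocation in three places.

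- **Study research design.** The unit is the school: "Secondary schools will be the unit of randomisation". The Abstract says the same.
- **Blinding and sampling technique, Step 2.** "Two comparable Local Government Areas (LGAs) in the project state will be selected using simple balloting". The LGA list is stratified by socio-economic status and urbanisation. The step then assigns the areas to arms: "One of the LGAs will be the experimental while the other will serve as the control".
- **Blinding and sampling technique, Step 3.** "Twenty two schools will be pair-matched based on their ownership (i.e. public and private) and population size", and these are "randomly allocated to either the experimental (11 schools) or control (11 schools) group by simple randomisation by an independent researcher". LGA is not named as a matching factor.

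Two other sections bear on this. Study site names two cities: "The study sites are Ibadan and Ogbomosho, urban cities located in Oyo State". Data management and statistical analysis plans mixed models for repeated measures, with random effects for city and school.

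**The concern.** Step 2 fixes a school's arm by its location. Step 3 fixes it by a random draw among schools. A team following Step 2 would run a two-area comparison; a team following Step 3 would run a cluster randomised trial with 11 clusters per arm. The two designs support different claims and need different standard errors.

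Under Step 2, anything that changes in one LGA and not the other during the 12 weeks or the follow-up would be read as an intervention effect. More schools or more students would not help, because the number of areas per arm stays at one. The sample size calculation carries only a school-level ICC and has no LGA component.

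**Working it through.** **1. Can both rules hold?**

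- If arm equals LGA, Step 3 has nothing left to allocate. It can only describe sampling matched schools inside each LGA.
- If Step 3 allocates schools, the arms will in general be mixed within LGAs, and the Step 2 sentence is untrue.
- Suppose every pair held one school from each LGA. Independent draws in 11 pairs give 2^11 = 2,048 allocations, and only 2 of them place each LGA wholly in one arm: 2/2,048 = 0.1%. Randomising schools would therefore almost never produce the Step 2 layout.

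**2. What each rule gives**

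| | Step 2 governs | Step 3 governs, one draw per pair |
|---|---|---|
| Allocation units per arm | 1 | 11 |
| Possible allocations | 2 | 2,048 |
| Smallest two-sided randomisation p-value | 2/2 = 1.0 | 2/2,048 = 0.001 |
| Degrees of freedom for between-LGA variance | 0 | arm not tied to LGA |

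The Step 2 column assumes that the choice of experimental LGA is itself random. The text describes balloting for selecting the two LGAs, not for deciding which is experimental.

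**3. Size of the problem if Step 2 governs (illustration)**

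The plan gives no figure for between-LGA variation, so there is none to reproduce.

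Inputs from the protocol article: school ICC 0.38, 11 schools per arm, 1000/22 = 45.45 students per school, two-sided 5% level, and proportions of 62% and 72% (mean 67%). Assumption: LGA holds a share L of outcome variance, with L between 1% and 5%.

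For a comparison of school means at follow-up only, in units of total variance:

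- Variance the school-level test allows for: V1 = 2 × [0.38 + (1 − 0.38 − L)/45.45]/11
- True variance of the arm contrast: V2 = V1 + 2L
- True size = 2 × P(t on 20 df > 2.086/√(V2/V1))

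L = 1%: V1 = 2 × (0.38 + 0.0134)/11 = 0.0715; V2 = 0.0915; ratio 1.28; true size 8.0%.

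L = 5%: V1 = 2 × (0.38 + 0.0125)/11 = 0.0714; V2 = 0.1714; ratio 2.40; true size 19.3%.

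A normal approximation, with school-level variance 2 × [0.38/11 + 0.62/500] on the same scale, gives 8.3% and 20.6%. Both methods put the range at about 8-20%.

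On the outcome scale, the standard deviation of a chance difference between two LGAs is √(2 × L × 0.67 × 0.33). This is 6.6 percentage points at L = 1% and 14.9 at L = 5%, against a planned effect of 72 − 62 = 10 points.

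**4. Does the planned analysis repair it?**

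Outcomes are measured at T0, T1 and T2. If the effect is read as change from baseline by arm, stable differences between the LGAs are largely removed. Area-specific change over time is not. A random effect for city does not help if the two cities are the two LGAs, because it would then coincide with arm. The document does not say whether they correspond.

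**The case against.** The best reply is that one sentence stands against several. The Abstract and the design section both name schools as the unit, Step 3 allocates them through an independent researcher, and a city random effect makes most sense if arm varies within city. On that reading the Step 2 sentence is a slip. This stands in part: a reader might infer that the trial is simply confounded with area, but the document supports that only if Step 2 governs.

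A reader might also infer that no analysis could separate intervention from area. That goes too far. The baseline measurements and repeated-measures model can deal with stable differences, and the LGAs are to be comparable on socio-economic status and urbanisation. Neither handles area-specific change or supplies replication at LGA level.

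A third tempting inference is that Step 3 contradicts itself by combining pair-matching, an 11/11 split and simple randomisation. It need not: a simple draw within each pair satisfies all three. The wording merits clarification only.

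The size figures are open to fair criticism. They rest on an assumed LGA share and a follow-up-only comparison, which is not the planned analysis. For the planned model the relevant quantity is how far LGAs differ in change over time, and the document gives no value for it.

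Finally, separating arms by area may be deliberate, to limit spill-over of a school-wide intervention. The protocol gives no such reason, but the possibility means the authors must say which rule they intend. The CONSORT flowchart is not shown and might indicate this, but it could not make both rules true.

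**Conclusion.** The contradiction is real on any reading: Steps 2 and 3 state different allocation units and nothing shown reconciles them. The consequence is conditional. If Step 2 governs, there is one unit per arm, area-specific change is inseparable from the intervention effect, and school-level standard errors are too small for the arm contrast. The illustrative true size of about 8-20% for a nominal 5% test assumes that LGA holds 1-5% of outcome variance, a school ICC of 0.38 and no use of baseline; it shows the order of the problem and does not predict the error rate of the planned model. If Step 3 governs, the confounding disappears and what remains is a false sentence in Step 2. The claim to be a cluster randomised trial depends on which rule applies, so the text has to be corrected.

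**What to change.** Since schools are the declared unit of randomisation:

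1. Delete the Step 2 sentence that gives each LGA an arm.
2. In Step 3, form the matched pairs within each LGA on ownership and population size. This needs an even number of schools per LGA, for example 5 pairs in one and 6 in the other.
3. State that the independent researcher makes one random draw per pair, and replace the reference to simple randomisation by randomisation within matched pair.

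The cost is a change of wording and an allocation list by pair; the numbers of schools and students stay the same. The drawback is that intervention and control schools would share an LGA, so some spill-over between them is possible.

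If allocation by LGA is intended, keep Step 2, stop describing the trial as randomised by school, and state that it compares two areas with one area per arm. That costs nothing in fieldwork but gives up the claim of replicated randomisation.
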